### Study 2: Comparing the roles of visuospatial perspective-taking and verbal interaction in developing theory of mind and emotion understanding

#### Participants

This study will compare the effects of three different training methods on the development of mind and emotion understanding in preschool children. Participants will consist of 120 typically developing Cantonese-speaking 4.5-year-olds (60 males; 60 females), with 40 children in each training group. We used G*Power 3.1 to conduct an a priori power analysis to determine the required sample size. Results indicated that a total sample of 98 participants was required to achieve a power of 0.80 for detecting a medium-to-large effect (*f* = 0.32) at an alpha of 0.05 for a MANOVA (MANOVA: Repeated measures, within-between interaction). To account for a potential attrition rate of 20%, we propose to recruit 40 children per group, thus 120 children in total, via electronic fliers on local internet groups.

#### Design, measures and procedures

The procedures will be similar to those in study 1. Written informed consent and information on family demographics, child characteristics, and executive functioning will be obtained from all participants’ parents or legal guardians prior to the initiation of the study. Children will be pre-tested and post-tested with the same battery of measures as those used in study 1. The training period will also be six weeks, with one 1.5-h training session per week. The training will be conducted in a child-friendly lab at the University. Upon completion of the training, the participants' parents or legal guardians will receive a report of their child's performances and a gift voucher valued at HKD$200.

#### Training activities

The children will be randomly grouped into pairs, and a trained experimenter will guide them. Like study 1, the experimenters will receive a three-hour training on the protocol, and their instructions and guidance will be regularly monitored. Children will be randomly assigned to one of three training groups, namely (a) *socialised altercentric block building*, (b) *parallel altercentric block building*, and (c) *paired dialogic reading*. Among the training groups, the socialised and parallel altercentric block building groups are based on the altercentric block building group in study 1. Both groups will also have the same gradation of difficulties in terms of model complexity and seating position as in study 1. The paired dialogic reading is derived from the conventional language-based training. The three different training activities are described below:

**Table Tabb:** 

Training groups	Training activities	Visuospatial perspective-taking	Verbal Interaction
(a) *Socialised altercentric block building* (Fig. 3)	Two children will be seated next to each other, and a toy bear will be seated at 180°, 90°, or 270° angular difference to the line of sight of the children. The experimenter will present a model figure built from blocks. Children will be asked first to reproduce the figure based on their own visual frame. Then, they will be asked to adopt the visual frame of the toy bear and reproduce the figure. Note that the children will be encouraged to discuss the perspective of the toy bear when building the block-figure. Therefore, both visuospatial perspective-taking and verbal interaction will be trained in this group	✓	✓
(b) *Parallel altercentric block building* (Fig. 3)	This training group will have the same procedures as that in the (a) socialised altercentric block building group, except children in this group are required to reproduce the block-figure without discussing the perspective of the figurine. Therefore, only visuospatial perspective-taking will be trained in this group	✓	✗
(c) *Paired dialogic reading*	The storytelling intervention by Ornaghi et al. [101] will be adapted in this training group. The experimenter will read the book series "The Adventures of Jack and Theo" [102] to the children. Children will listen to three stories in each session. After each story, children will be engaged in different language games and conversations. This training will minimize the use of the mental state lexicon to avoid perspective-taking and mentalising. No block-building activity will be involved in the training group. Therefore, only verbal interaction will be trained in this group	✗	✓

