The main goal of study 2 is to determine whether visuospatial perspective-taking or conventional verbal training is more effective in enhancing children’s mind and emotion understandings. ToM training has mostly been heavily language-based because the literature has identified language as a strong correlate of ToM development [42, 44]. Visible social interaction without language input does not promote false-belief understanding. Hence verbal interaction is regarded to be crucial to mind understanding [88]. Moreover, a study by Lohmann and Tomasello [44] involving 3-year-old children also found that training on the theory of mind with minimal linguistic interaction was ineffective in improving children’s false belief understanding. On the basis of the embodiment framework, study 2 will investigate whether simulating the visuospatial experiences of others alone, i.e. *without* the presence of verbal communication, is sufficient to enhance mind and emotion understanding. By doing this, study 2 will compare the training effect caused by visuospatial perspective-taking to the one caused by mere verbal interaction. In study 2, children aged 4.5 years will be randomly assigned to participate in either (a) *socialised altercentric block building* (both visuospatial perspective-taking and verbal interaction), (b) *parallel altercentric block building* (visuospatial perspective-taking only), or (c) *paired dialogic reading* (verbal interaction only). Dialogic reading will be served as a promising interactive approach because this training involves back-and-forth verbal exchanges between children. In addition, dialogic reading is easy to administer with preschool children. The differences between groups in ToM and emotion understanding post-training would indicate whether visuospatial perspective-taking or verbal interaction group will be more effective in fostering mental state understandings. Two research questions will be addressed in study 2:

(1) What is the difference between the effect of visuospatial perspective-taking vs. general verbal interaction training on improving preschoolers’ ToM and emotion understanding?

(2) Do children trained in the socialised altercentric block building group improve significantly more than children in the parallel altercentric block building and paired dialogic reading groups in ToM and emotion understanding after 6 weeks of training?

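### Study 2's parallel arm bars one topic of talk, which is narrower than the no-verbal-communication condition it is meant to create

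*Protocol article*

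**What the plan says.** The aim is in the section The present study. Study 2 asks whether simulating another's visuospatial experience alone, without "the presence of verbal communication, is sufficient to enhance mind and emotion understanding". The same paragraph states the contrast: "study 2 will compare the training effect caused by visuospatial perspective-taking to the one caused by mere verbal interaction". Research question 1 puts it as "visuospatial perspective-taking vs. general verbal interaction training".

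The arms are defined in the table under Study 2, Training activities:

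- **(a) Socialised altercentric block building.** Two children sit side by side, reproduce a block figure from their own view and then from a toy bear's, and are encouraged to talk about the bear's perspective. Ticks for perspective-taking and for verbal interaction.
- **(b) Parallel altercentric block building.** "This training group will have the same procedures as that in the (a) socialised altercentric block building group", with one exception: "children in this group are required to reproduce the block-figure without discussing the perspective of the figurine". From this the table concludes: "Therefore, only visuospatial perspective-taking will be trained in this group". Tick for perspective-taking, cross for verbal interaction.
- **(c) Paired dialogic reading.** Three stories a session, each followed by language games and talk. "This training will minimize the use of the mental state lexicon to avoid perspective-taking and mentalising". Cross for perspective-taking, tick for verbal interaction.

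For all arms, "The children will be randomly grouped into pairs, and a trained experimenter will guide them".

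The Study 2 Data analysis plan predicts that (b) will raise perspective-taking but not general language ability. It expects the results to show whether perspective-taking helps ToM over and above what verbal interaction contributes.

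**The concern.** The condition named in the aim and marked in the table is the absence of verbal communication. The rule that implements it removes one subject of conversation. These are different conditions, and both Study 2 questions rely on the arm that the rule defines.

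The verbal factor also differs in kind across the arms. In (a) it is talk about the bear's perspective; in (c) it is talk that keeps away from perspective and mental states. Removing the first kind from (b) does not by itself make (b) free of the second.

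The protocol motivates Study 2 with earlier work in which interaction or training with little or no language did not improve false-belief understanding. A gain in (b) would speak against that work only if (b) really lacked verbal interaction. If the rule does not secure this, the analysis cannot separate the ingredients afterwards.

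**Working it through.** No figure in the plan is in dispute here, so the check sets the passages side by side.

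1. **Condition intended for (b).** The present study: no verbal communication. Training-group table: cross for verbal interaction. The two agree.
2. **Rule that creates it.** Same procedures as (a), except no discussion of the figurine's perspective. A definition of the form same-as-(a)-except carries everything else in (a) over to (b): two children side by side, in a pair, with a guiding experimenter. The one stated exception concerns a topic.
3. **Does 2 imply 1?** No. A pair that never mentions the bear's view but talks about the blocks or each other's building complies with the rule as written and still has verbal interaction. The table's conclusion that only perspective-taking is trained does not follow from the rule alone.
4. **Consequences for the contrasts.**
   - (b) versus (c), research question 1. Intended: perspective-taking versus verbal interaction. Secured by the text: perspective-taking with an uncontrolled amount of other talk versus structured reading and talk.
   - (a) versus (b), part of research question 2. Intended: the addition of verbal interaction. Secured by the text: the addition of discussion of perspective.
   - (a) versus (c), the other part of research question 2. The (b) rule does not enter this comparison.
5. **Consequence for the inference.** The Data analysis plan's conclusion about perspective-taking over and above verbal interaction needs an arm without verbal interaction. Only (b) is labelled that way.

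**Sample size.** The Study 2 figure is sound for its inputs. For the within-between interaction with 3 groups and 2 occasions, df1 = 2, df2 = N − 3 and λ = f²N. With f = 0.32 and N = 98, λ = 0.1024 × 98 = 10.04, df2 = 95, and power at alpha 0.05 is 0.804, so the stated 98 is reproduced.

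**Size of the effect.** The documents give no amount of talk in any arm, so any dilution is an assumption. If shared talk cut the omnibus f by 10%, 25% or 50%, power at N = 98 would be 0.71, 0.54 or 0.27. This only shows sensitivity. It is not an estimate, it concerns the three-group test rather than a pairwise contrast, and the documents do not fix even the direction in which stray talk would move each contrast.

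**The case against.** The best case for the plan is that silence is not permission. The article says nothing about other talk in (b). The name parallel and the cross both signal that peer interaction was meant to be excluded. Experimenters are trained on a session protocol that is not shown, and the figure of the two block arms is missing too; either could restrict talk further. The table can also be read as saying that verbal interaction is not a trained component, not that the room is silent.

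Much of this stands, and it rules out several stronger readings that a reader might infer:

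- *All other talk is allowed in (b), so the arm fails to deliver its condition.* The text does not say so. It supports only that the rule as written does not secure the condition.
- *(b) contains the reading treatment.* It has none of the stories or language games of (c). Only the general kind of talk, conversation not about perspective, is left unaddressed.
- *The experimenter's spoken instruction confounds the block arms.* The instruction belongs to procedures that (a) and (b) share, so it cannot explain a difference between them. The protocol also describes the verbal element of dialogic reading as two-way talk between children, which an instruction is not.
- *The amount of stray talk can be bounded from session length.* Six sessions of 1.5 h give 9 h of contact, but nothing says how much of it is talk.

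Two safeguards count in the plan's favour but do not close the gap. Expressive vocabulary is tested before and after training, and (b) is predicted not to raise language ability; that is an outcome-level check and does not measure talk during sessions. Study 2 monitors experimenters' instructions and guidance, but the article does not say that the children's own talk is assessed.

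What the objection does not answer is that the published rule is specific and narrower than the published aim. Evidence of intent shows what the rule should achieve, not that it does.

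**Conclusion.** The point holds in a limited form. The parallel arm's rule, as written, is narrower than the condition claimed for it in the aim and in the table. Two of the Study 2 contrasts therefore do not carry the interpretation placed on them: parallel versus reading is not cleanly perspective-taking versus verbal interaction, and socialised versus parallel isolates discussion of perspective.

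The consequence is for interpretation, and its size cannot be calculated from the documents. The conclusion rests on the article's wording and assumes that no unseen session protocol adds a rule on peer talk. If one does, the remedy is simply to state it, because the published passages would still need to agree. The change should be made before training starts; it is not a fatal flaw, and the randomised comparison of the three packages remains valid as a comparison of packages.

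**What to change.** Reconcile The present study, the Study 2 training-group table and the Study 2 Data analysis plan in one of two ways.

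1. **Tighten the arm.** Change the rule for (b) to no conversation between the children during building. Keep every other procedure and the experimenter's instructions identical to (a), so that peer conversation is the only difference. Check adherence within the monitoring already planned, by adding children's talk as an item. Since instructions remain spoken, the aim should say without peer conversation rather than without verbal communication.
2. **Narrow the claim.** Keep the rule for (b) and restate the aim, the table's cross and the over-and-above inference as concerning training without discussion of perspective. Parallel versus reading is then described as a comparison of two training packages.

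The first option keeps more of the scientific question. It costs a change of wording, a line in the experimenters' training and a simple adherence item. Full silence is not achievable at 4.5 years, so the claim becomes slightly narrower even then. The second option costs only wording but gives up the statement about perspective-taking without verbal interaction. Neither changes the sample size or the planned tests.

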### Theory of mind and language

Language ability has been consistently found to be associated with ToM performance [11, 26–30]. In particular, children’s understanding of mental state vocabulary, such as *think, believe, want, know*, and sentential complements such as “John believes/says it is raining” are linked to their ToM scores [29, 31–33]. There have been two main explanations for this relationship between ToM and language ability [11]. From the perspective of linguistic determinism, researchers argue that language plays a causal role in the development of ToM ability. In other words, children who lack language ability do not achieve ToM [31, 34]. However, there is much controversy over language's specific role in ToM development [26]. The domain-general perspective argues that the majority of the ToM tasks are verbal tasks and thus language is heavily needed in mental state understanding [35, 36].

A number of social-environmental factors have been found to be associated with children’s ToM development, including family size and the number of siblings [37–39], socioeconomic status [2], child’s sociolinguistic awareness [40], mother’s mind-mindedness [41], and mother–child mental state talk [6, 8]. These factors create a social-linguistically enriched environment for children to explore others’ mental stances and perspectives, and as such, children can respond appropriately to social interactions by inhibiting their egocentric perspective. Linguistic scaffolding from elder siblings and parents thus strengthens a child’s capacity to apprehend the abstract mind. From this, we can see that language ability and verbal interaction are essential to developing mind understanding, such as the ability to relate the actions of others to their mental states. This may contribute to the fact that existing ToM training is heavily language-based [42–44]. These language-based ToM training were explicitly designed to teach children mentalistic language and knowledge of inner states through role-playing and story-telling.

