## Discussion

This study proposes a novel visuospatial-based block-building training to complement the conventional ToM training. The findings are expected to have theoretical and practical implications. Theoretically, this research may advance our knowledge of the nature of mental state understanding in two ways: First, if our findings show that ToM and emotion understanding can be improved by training then this will give credence to the idea that individual variations in mental state understanding are not entirely the result of maturational or developmental cognitive processes, but are partially driven by social-environmental input. More notably, the proposed visuospatial-based training will be directly compared to the traditional language-based training, which addresses the contrasting theoretical accounts of social-cognitive development. To date, the dominant view has been that language and verbal interaction is the basis of ToM development. This study draws on the embodied cognition literature to explore the possibility that mind and emotion understanding may be influenced by our simulation of another person’s visuospatial experiences. The findings of this research may shed new light on how mind understandings develop and may further bridge the conceptually related but empirically isolated literature of ToM and visuospatial perspective-taking.

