The study also has direct practical implications. There has been a wealth of evidence that early mental state understanding strongly predicts positive child outcomes, including social competence and academic performance [103–108]. As a result, researchers may collaborate with practitioners to develop evidence-based training to increase mind and emotion understanding. To date, ToM training has predominantly relied on verbal interaction. ToM training generally involves specific training in language (such as understanding sentential complements and mental state terms) or explicit conversation regarding mental states and the relationship to behaviour. Paradoxically, ToM interventions often target children with autism spectrum disorder (ASD), who commonly have oral language deficits. This place children with ASD under challenging circumstances. In that light, the present study proposes new avenues to train psychological perspective-taking, supposing the results will indicate that visuospatial perspective-taking in the form of block building is a feasible and effective training paradigm. In that case, this specific block-building training can be introduced to complement the conventional ToM training. Block play is popular among young children, especially children with ASD. The proposed block-building activities ought to be attractive to them. Moreover, as blocks are always accessible in kindergarten classrooms, this proposed block-building training may be implemented in regular early childhood education settings to improve young children’s ToM and emotion understanding.

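### Study 2 is presented as a comparison with conventional language-based theory-of-mind training, but its reading arm minimises mental-state language, so its claims should be limited to general verbal interaction

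*Protocol article*

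**What the plan says.** **The claim.** The section on the present study gives the main goal of Study 2 as to "determine whether visuospatial perspective-taking or conventional verbal training is more effective in enhancing children’s mind and emotion understandings". The Discussion says that "the proposed visuospatial-based training will be directly compared to the traditional language-based training" and that this bears on the competing theoretical accounts. The Study 2 training activities section adds: "The paired dialogic reading is derived from the conventional language-based training".

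**What conventional training is.** The Background section on theory of mind and language describes existing language-based trainings as "explicitly designed to teach children mentalistic language and knowledge of inner states through role-playing and story-telling". The Discussion describes such training again: specific language work, including mental-state terms, or "explicit conversation regarding mental states and the relationship to behaviour".

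**What the arms contain.** For the paired dialogic reading arm (c), the training table states: "This training will minimize the use of the mental state lexicon to avoid perspective-taking and mentalising". For the socialised block-building arm (a), it states that "the children will be encouraged to discuss the perspective of the toy bear when building the block-figure". The parallel block-building arm (b) follows the same procedures as (a) but without that discussion. The table credits (a) with perspective-taking and verbal interaction, (b) with perspective-taking only, and (c) with verbal interaction only.

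**The intended inference.** The Study 2 data analysis plan ends by saying the result will reveal whether perspective-taking helps theory of mind over and above what verbal interaction contributes.

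**The concern.** The article gives two descriptions of one comparator that do not fit together. In the stated goal and the Discussion it is the conventional, language-based approach. In the training table it is a reading programme designed to keep down the mental-state content by which the article characterises that approach. If a block-building arm did better, a report following the stated goal would say it had outperformed established training, when that training had not been tested.

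The second issue concerns the closing inference. To show an effect of perspective-taking over and above verbal interaction, verbal interaction should be comparable in both arms while perspective-taking varies. The only pair with verbal interaction ticked on both sides is (a) and (c), and there the talk itself differs. An advantage for (a) could come from talking about another's viewpoint, which is close to the language account the study sets out to challenge.

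**Working it through.** No figure in the plan bears on this point. The stated Study 2 sample size does reproduce: with 3 groups, 2 time points, f = 0.32 and alpha 0.05, df1 = 2, df2 = 98 − 3 = 95 and λ = 98 × 0.32² = 10.04, which gives power 0.804. But sample size cannot change what a contrast identifies. The check is a comparison of the article's statements.

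**Step 1: is the comparator the training it is said to be?**

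| Source | Mental-state content |
|---|---|
| Background, theory of mind and language | Central: mentalistic language and inner states are taught |
| Discussion, practical implications | Central: mental-state terms, or explicit talk about mental states |
| Study 2 training table, arm (c) | Deliberately minimised |

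The component that characterises conventional training is the one the reading arm is designed to limit. Arm (c) can stand for general verbal interaction, not for conventional training.

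**Step 2: what does each contrast change?**

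| Arm | Block building | Visuospatial perspective-taking | Talk |
|---|---|---|---|
| (a) Socialised | Yes | Yes | Discussion of the bear's perspective |
| (b) Parallel | Yes | Yes | No perspective discussion |
| (c) Reading | No | No | Stories, language games and conversation with minimal mental-state content |

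- (a)−(b): one component changes, the perspective discussion. It isolates talk, not perspective-taking.
- (b)−(c): perspective-taking block play against general verbal interaction. This matches research question 1. Block play also differs, but the perspective-talk imbalance does not arise because (b) has no such discussion.
- (a)−(c): perspective-taking, block play and content of talk all change. Three differences enter one contrast, which cannot separate them.

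**Step 3: does the closing inference follow?** If it rests on (a)−(c), it does not follow from that contrast alone, because perspective-taking is not separated from perspective talk. If it rests on (b)−(c), it compares two different activities, and the verbal interaction in question is the general, non-mentalistic kind.

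**Step 4: direction.** The Background reports that training with explicit conversation about mental states appeared to have a significant impact on theory of mind. On that account, limiting such talk in (c) while encouraging perspective discussion in (a) would tend to favour (a). The article gives nothing from which to put a size on this.

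**The case against.** The strongest reply is that the operative question already fits the arm. Research question 1 sets perspective-taking against general verbal interaction, and the abstract labels the arm as verbal interaction only. For that question, keeping mentalising out of the reading arm is deliberate, disclosed and necessary; otherwise (c) would also train perspective-taking. Research question 2 asks only whether the socialised group improves more than the other two, and a package comparison answers that as posed. The abstract and Discussion also speak of complementing conventional training, not replacing it.

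All of this stands, and it shows that the arm is sound for the narrower question. It does not rescue the stated main goal or the Discussion's direct-comparison claim.

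Several stronger readings are tempting but not supported:

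- *That mental-state language is removed from the reading arm, or that the arm is inert.* The table says minimised, and the data analysis plan predicts improvement in all three arms.
- *That every Study 2 comparison is tilted towards block building.* The talk imbalance concerns (a)−(c) only and does not touch (b)−(c).
- *That bias in favour of the new training is established.* The talk in (a) is about a toy bear's visual frame, and the table does not say that it uses mental-state vocabulary.
- *That block play is wholly uncontrolled.* Study 1 compares altercentric with egocentric block building, so block play is present in both its arms. This partly answers the block-play point across the programme, but Study 1 has no reading arm and cannot separate perspective-taking from perspective talk in (a)−(c).
- *That the statement of the reading arm's origin is false.* Being derived from conventional training does not mean being identical to it. The reading arm adapts a cited storytelling intervention that is not available here, so how far it departs from that source cannot be judged.

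**Conclusion.** The concern holds in limited form. Study 2 can compare perspective-taking with general, largely non-mentalistic verbal interaction. It cannot support a conclusion about conventional language-based theory-of-mind training, which the goal and the Discussion both promise. Separately, (a)−(c) is a package comparison and cannot on its own show an effect of perspective-taking over and above verbal interaction.

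The size of any distortion is not estimable from the article. That its direction probably favours (a) is an inference. It assumes that the arms are delivered as the table describes, and that perspective discussion acts in a similar way to the mental-state talk the Background treats as effective. The mismatch between label and content depends on neither assumption. It deserves correction because it affects the study's main stated goal and its headline theoretical conclusion.

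**What to change.** 1. In the section on the present study and in the Discussion, replace the labels *conventional* and *traditional language-based* for the Study 2 comparator with *general verbal interaction with minimal mental-state content*. Draw no conclusion about superiority to conventional theory-of-mind training.
2. In the Study 2 training activities section, keep the statement of the reading arm's origin but add that its mental-state content is minimised.
3. In the Study 2 data analysis plan, tie each conclusion to its contrast: (a)−(b) estimates the effect of adding perspective discussion; (b)−(c) compares perspective-taking block play with general verbal interaction; (a)−(c) is a package comparison.
4. Keep the closing inference of that plan but qualify it: the verbal interaction meant is general and non-mentalistic, and (a)−(c) does not separate perspective-taking from perspective talk.

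The cost is a narrower claim. No arm, measure or sample size changes.
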